## Abstract

**Background:**

Within the last decade there has been a growth in the call-centre industry in the UK, with a growing awareness of the voice as an important tool for successful communication. Occupational voice problems such as occupational dysphonia, in a business which relies on healthy, effective voice as the primary professional communication tool, may threaten working ability and occupational health and safety of workers. While previous studies of telephone call-agents have reported a range of voice symptoms and functional vocal health problems, there have been no studies investigating the use and impact of vocal performance in the communication industry within the UK. This study aims to address a significant gap in the evidence-base of occupational health and safety research. The objectives of the study are: 1. to investigate the work context and vocal communication demands for call-agents; 2. to evaluate call-agents' vocal health, awareness and performance; and 3. to identify key risks and training needs for employees and employers within call-centres.

**Methods and design:**

This is an occupational epidemiological study, which plans to recruit call-centres throughout the UK and Ireland. Data collection will consist of three components: 1. interviews with managers from each participating call-centre to assess their communication and training needs; 2. an online biopsychosocial questionnaire will be administered to investigate the work environment and vocal demands of call-agents; and 3. voice acoustic measurements of a random sample of participants using the Multi-dimensional Voice Program (MDVP). Qualitative content analysis from the interviews will identify underlying themes and issues. A multivariate analysis approach will be adopted using Structural Equation Modelling (SEM), to develop voice measurement models in determining the construct validity of potential factors contributing to occupational dysphonia. Quantitative data will be analysed using SPSS version 15. Ethical approval is granted for this study from the School of Communication, University of Ulster.

**Discussion:**

The results from this study will provide the missing element of voice-based evidence, by appraising the interactional dimensions of vocal health and communicative performance. This information will be used to inform training for call-agents and to contribute to health policies within the workplace, in order to enhance vocal health.

## Background

Research to date has failed to account for the central and most important tool for the communications industry, the human voice. Failure to investigate the use and impact of vocal performance has resulted in a significant gap in the evidence-base of occupational health and safety research. Voice is not simply the tool for communication transmission, it is directly related to the working ability and efficiency of the single most sought after attribute sourced by employers in the industry – effective verbal communication and interaction [1].

There is substantial epidemiological and physiological evidence supporting the view that groups such as teachers, singers, lawyers, and telemarketing workers are at risk of occupational health and safety voice problems [2,3], in particular, those working in call-centre environments [3]. Furthermore, majority of these studies include small participant numbers. The Department of Trade and Industry report [1] provided one of the most comprehensive reviews of the call-centre industry across the UK. Within the UK in 2003, there were 5,320 contact-centres and almost 500,000 agent positions, and this industry is forecast to continue to increase. A range of occupational safety and health (OSH) issues were identified as potential risks of current stressors in this work environment, raising the importance of regular appraisal and review of the impact of these issues on the health and economic well-being of the industry. Health and Safety Executive (HSE) [4] provided further focus, with an indepth investigation of stress and psychosocial stressors in the call-centre industry. Potential hazards were highlighted, related to vocal, optical, auditory and musculoskeletal health. Vocal health was evaluated by self-report of the frequency of symptoms, 'some, most or all of the time', with 39% reporting hoarseness; 32% pitch change and 42% discomfort in the throat. The report suggests that existing risks can be controlled through good work design and the provision of information and training. However, the contributory physiological demands have not been fully evaluated in relation to the physical work environment.

Vilkman [5] states that the prevention and treatment of occupational voice disorders required improved OSH arrangements. Vocal strain was classified as 'repeated movements (and collisions) of the vocal folds' as a potential repetition strain injury (RSI). The occupational medicine definition of RSI is 'overload of repetitive movements and static and dynamic muscle loading combined with biomechanical, ergonomic and psychological factors as well as poor treatment of early symptoms' [6]. As vocal abnormality refers to the person's ability to cope with the working tasks, reliable and valid tools for reporting on voice complaints are important [5].

Call-centre workers have prolonged voice use and heavy vocal loading, thus increasing the risk of occupational dysphonia, which is a voice disorder due to work-related overuse or abuse that threatens communicative, interactive and economic efficiency [2,5,7,8]. Vocal loading may be attributed to prolonged voice use, and the work environment, where background levels of voice may affect the quality, type and loudness of phonation in speech. Jones et al [9] compared the prevalence of voice problems among telemarketers compared to the general population and concluded that they were twice as likely to report one or more symptoms of vocal strain compared with controls. In addition, impaired work productivity due to voice problems occurred in 31% of the telemarketers surveyed. Lehto [10] identified risk factors in voice professions as: background noise, poor air quality (dryness, dust), poor posture and vocal loading.

Risks to vocal performance and efficiency are not simply physiological, but in telephone interaction, also demand co-ordination of optimum psychological, behavioural and environmental settings to maintain an efficient balance for the interaction. Clearly, subtle paralinguistic vocal changes may unconsciously affect the call-agent, but also the receiver negatively. Cameron [11] describes the demands of this work environment as emotional, cognitive and vocal. Furthermore, the focus of training and quality monitoring has been vocal styling and not skilling for the task. Lehto [12] suggests that when the call-agent's voice becomes strained, hoarse or effortful, this in turn adds physiological and cognitive stress which can result in less efficient interaction, particularly when following a script or protocol for calls.

Vast resources have already been spent without fully understanding or appreciating the interactional dimensions of telephone communication – physical, environmental, behavioural and psychosocial aspects of vocal communication. However, there have been no studies investigating the use and impact of vocal performance in the communication industry within the UK. This study aims to address this significant gap in the evidence-base of occupational health and safety research. This research will therefore provide the missing element of voice-based evidence, by appraising and ranking the interactional dimensions of vocal health and communicative performance.

The objectives of the study are:

1. To investigate the work context and vocal communication demands for call-agents;

2. To evaluate call-agents' vocal health, awareness and performance;

3. To identify key risks and training needs for employees and employers within call-centres.

## Methods and design

### Research design

This research will take the form of an occupational epidemiological study. This will be a mixed methods design, comprising a qualitative and large-scale quantitative approach, including acoustic measurement in the naturalistic work environment. There are three stages of this research study: 1. interviews with a senior manager (eg Call-centre or Human Resources Manager) within the call-centres; 2. online survey; and 3. acoustic measurements.

### Participants

The research participants will be employees from call-centres throughout the UK and Ireland. As this is a relatively new area of research, the main measurement tool, biopsychosocial questionnaire for the online survey will be developed to collect the relevant information to meet the aim and objectives of this study, thus power calculations were not calculated. The sample sizes of the participants in each stage of this study are as follows: 1. interviews with one manager from each participating call-centre (at least 10 call-centres); 2. online survey will be completed by a purposive sample of at least 500 call-agents from the participating call-centres; and 3. acoustic measurements will be conducted from at least 10% of participants from stage 2. It is anticipated that these sample sizes should be sufficient for the measurement tools to collect information on the vocal demands, communication, vocal health and training needs of call-agents in call-centres within the UK and Ireland. The findings from this study will be used to calculate a power calculation for the follow-up randomised controlled trial in call-centres.

The Human Resource department of each call-centre in the UK and Ireland will be contacted via e-mail inviting participation in this research study. Interested call-centres will contact the research team and receive full details of this study, and a manager from the participating organisations will provide written informed consent. The management team within the participating call-centres will inform their call-agents of this study and invite them to complete the online survey. The first question on the questionnaire for the online survey will ask the call-agents to indicate consent.

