### Data analysis

The data from the interviews will be transcribed and analysed thematically to determine context and process characteristics of each organisation. Qualitative content analysis will identify underlying themes and issues, which will be used to further refine and inform the questionnaire design.

Questionnaire analysis will account for the complex interaction of multi-factorial variables and the wide range of theoretical perspectives requiring evaluation with an appropriate range of methodological tools and approaches. Given the complexity of the study and the array of variables impacting on vocal strain, there is a need to employ sophisticated forms of analysis, with the capacity to explore potential directional effects across a wide range of variables. While multiple regression analysis is frequently used to analyse social science data, the main problem is handling measurement error, indirect or mediating effects. Since most multivariate procedures cannot deal with multiple variables, particularly multiple dependent or criterion variables, hypothesis testing is difficult.

Therefore, the study will adopt a multivariate analysis approach using Structural Equation Modelling (SEM), to develop voice measurement models in determining the construct validity of potential factors contributing to Occupational Dysphonia [16]. The research design and associated analysis will therefore attempt to overcome the traditional complications of multiple indicators, indirect effects and measurement error by using structural equation modelling with latent variables and LISREL (Linear Structural Relations) estimation. SEM is a statistical methodology that takes a confirmatory (ie hypotheses-testing) approach to the multivariate analysis of a structural theory bearing on some phenomenon, representing causal processes, which generate assumptions on multiple variables [15]. The hypotheses are: 1. Call-agents' physiological voice production is improved with good vocal-working environment; 2. Call-agents' acoustic voice production is improved with good vocal-working environment; 3. Call-agents' psychosocial health is improved with good vocal-working environment. The relationships and effects of these aetiological indicators on the 'risk' of occupational dysphonia will be explored in order to determine the relative significance of physiological, behavioural environmental and psychological indicators at varying levels of severity.

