Acoustic analysis will be conducted on a random sample of the voice of call-agents from call-samples using the Multi Dimensional Voice Program (MDVP), which is a software programme that provides a robust multi-dimensional analysis of voice with graphic and numerical presentation of analysis [17]. MDVP is the gold standard measurement tool for quantitative analysis of voice. From the telephone call-samples, three sections each consisting of three seconds of the call-agent's continuous voice uninterrupted by the customer will be selected during 10 seconds at the first, middle and the end of the call. Three seconds of recording is within the recommended range for acoustic analysis by the manufacturer of the voice analysis software [17]. Therefore three sections (start, middle and end) of each call-sample will be used for acoustic analysis. The voices of the call-agents in these sample-calls will be analysed for the following 14 acoustic parameters: Mean Fundamental Frequency (MFo); Highest Fundamental Frequency (Fhi); Lowest Fundamental Frequency (Flo); Standard Deviation of Fo (STD); Amplitude Tremor Frequency (Fatr); Absolute Jitter (Jita); Jitter Percent (Jitt); Shimmer in dB (ShdB); Shimmer Percent (Shim); Peak-to-Peak Amplitude Variation (vAm); Noise to Harmonic Ratio (NHR); Degree of Voice Breaks (DVB); Degree of Sub-harmonics (DSH); and Degree of Voiceless (DUV). In addition, the acoustic results will be integrated into the voice measurement model using SEM.

All numerical data will be analysed using SPSS version 15. Descriptive statistics will include means, standard deviations and ranges for each variable from the online survey and acoustic analysis. Inferential statistics such as Pearson Correlations will be used to compare the objective and subjective measures. If the assumptions for the above parametric tests are violated then the appropriate non-parametric tests such as the Mann-Whitney will be used.

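### Call-agents are nested in call-centres, but the named analyses leave the centre out; run in their ordinary form they would understate the error of the survey-based environment effects

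*Protocol article*

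**What the plan says.** **Sample (Protocol article, Participants).** Stage 1 is "interviews with one manager from each participating call-centre (at least 10 call-centres"). In stage 2 the "online survey will be completed by a purposive sample of at least 500 call-agents from the participating call-centres". In stage 3 "acoustic measurements will be conducted from at least 10% of participants from stage 2". Centres volunteer, and then "The management team within the participating call-centres will inform their call-agents of this study and invite them to complete the online survey". On sample size the section says "thus power calculations were not calculated". It adds a later use of the data: "The findings from this study will be used to calculate a power calculation for the follow-up randomised controlled trial in call-centres".

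**Exposure and hypotheses (Data analysis).** Hypothesis 1 is that call-agents' "physiological voice production is improved with good vocal-working environment". Hypotheses 2 and 3 put acoustic voice production and psychosocial health in place of the outcome and keep the same exposure. According to Research procedures, the work environment is captured by the agents' online questionnaire.

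**Analyses (Data analysis).** The main method is a latent-variable structural equation model (SEM) with LISREL estimation. "All numerical data will be analysed using SPSS version 15", with Pearson correlations between the objective and the subjective measures, and tests such as Mann-Whitney as the fallback. The section explains why it chose SEM (multiple indicators, indirect effects, measurement error). It names no centre effect, second level, cluster-robust error or ICC.

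**The concern.** Agents in one centre work under the same management, often in the same rooms. The Background lists four risk factors for professional voice users. Background noise and poor air quality are plausibly common to a site, while posture and vocal loading differ between people. If both exposure and outcome are alike within a centre, agents do not count as independent observations of the link between them. For the part of the exposure that varies only between centres, the replication is the number of centres.

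An SEM or rank test in its ordinary form takes no account of this, and its standard errors for environment effects come out too small. The third objective is to identify key risks for employees and employers, and the Discussion expects guidelines to follow. Chance differences among a few volunteer centres could then be reported as workplace hazards. The follow-up trial would also need an ICC if it randomises whole centres, and the article names none as an output.

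**Working it through.** The article states no power, alpha, effect size or ICC, so there is no figure of its own to reproduce. The question is how far an ordinary agent-level analysis would go wrong.

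**Inputs from Participants.** At least 10 centres and at least 500 agents, so 500/10 = 50 agents per centre at both minima. Acoustic subsample: 10% of 500 = 50 agents, or 5 per centre.

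**Assumptions.** Two-sided nominal 5% test; equal centre sizes; outcome ICC (ICC_y) of 0.01, 0.05 or 0.10; share of exposure variance between centres (ICC_x) of 1, 0.5 or 0.2.

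**Formulas.**
- Design effect: DE = 1 + (m − 1) × ICC_y × ICC_x, with m agents per centre
- True SE / naive SE = √DE; effective n = N/DE
- True type I error of the naive test = 2 × [1 − Φ(1.96/√DE)]

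**Hypotheses 1 and 3 (survey, m = 50).** Example: ICC_y = 0.05 and ICC_x = 1 give DE = 1 + 49 × 0.05 = 3.45, √3.45 = 1.86 and effective n = 500/3.45 = 145. The type I error is 2 × [1 − Φ(1.96/1.86)] = 0.29.

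| | ICC_y 0.01 | ICC_y 0.05 | ICC_y 0.10 |
|---|---|---|---|
| ICC_x = 1: DE | 1.49 | 3.45 | 5.90 |
| true SE / naive SE | 1.22 | 1.86 | 2.43 |
| effective n | 336 | 145 | 85 |
| type I error | 0.11 | 0.29 | 0.42 |
| ICC_x = 0.5: DE | 1.25 | 2.23 | 3.45 |
| type I error | 0.08 | 0.19 | 0.29 |
| ICC_x = 0.2: DE | 1.10 | 1.49 | 1.98 |
| type I error | 0.06 | 0.11 | 0.16 |

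Simulating the naive correlation test (4,000 data sets per setting) gave 0.115 / 0.300 / 0.423 for ICC_x = 1, 0.072 / 0.175 / 0.267 for 0.5 and 0.059 / 0.101 / 0.154 for 0.2. This agrees well with the formula.

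**More centres, still 500 agents, ICC_x = 1 (simulated).** 25 centres of 20: 0.078 / 0.163 / 0.276. 50 centres of 10: 0.065 / 0.102 / 0.143.

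**Unequal centres.** With a coefficient of variation of 0.5 in centre size, DE = 1 + [(0.25 + 1) × 50 − 1] × ICC_y = 1.61 / 4.08 / 7.15.

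**Hypothesis 2 (acoustic, m = 5, ICC_x = 1).** DE = 1 + 4 × ICC_y = 1.04 / 1.20 / 1.40. The true SE is 1.02 / 1.10 / 1.18 times the naive one, and the type I error is 0.055 / 0.074 / 0.098.

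**Pearson correlations of objective with subjective measures.** These need the acoustic data, so m = 5 again. If both measures have an ICC of 0.10, DE = 1 + 4 × 0.10 × 0.10 = 1.04, which is negligible.

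**The case against.** The strongest reply is that the article never says agents are treated as independent. It specifies no level and no standard-error method for the SEM, and it condenses a fuller plan that may deal with clustering. That much stands: independence is what the named methods assume in their ordinary form, not something the plan declares. But the article goes into detail on why it chose the model and names specific tests, all without the centre. It also judges the sample sizes sufficient without considering how many centres inform an environment effect. A later analysis plan can adjust standard errors but cannot add centres. Responses are anonymous and coded, and the article does not say whether the code identifies the centre.

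A reader might infer several stronger things that the article does not support:

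- *That standard errors are far too small for all three hypotheses.* Hypothesis 2 rests on about 5 agents per centre, where the effect is small to modest.
- *That the environment is essentially a centre property.* Each agent reports it, and two of the four cited risk factors are personal. The figures for ICC_x = 1 are the upper end.
- *That there will be about 10 centres.* Ten is a floor, and centres throughout the UK and Ireland are to be invited. Equally, 500 agents is a floor, and more agents in the same 10 centres would raise the design effect.
- *That the Pearson correlations test the hypotheses.* They are stated only for objective against subjective measures.
- *That the detectable correlation at 80% power worsens from 0.125 (500 independent agents) to 0.79 (10 centres).* The second is a correlation of centre means, the first of individual agents. Put on the agent scale, 0.79 becomes about 0.21 to 0.40 for ICCs of 0.01 to 0.10, so the contrast should not be used.
- *That the follow-up trial's sample size will be wrong.* The article does not say that centres will be randomised, and nothing prevents an ICC from being estimated.

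**Conclusion.** The point holds for the survey-based hypotheses 1 and 3. The sample is nested by design, the exposure is plausibly shared in part within centres, and the named analyses leave the centre out. Applied in their ordinary form at the stated minima, they would be anti-conservative for environment effects, from slightly (type I error about 0.06) to severely (0.42). Where the study falls in that range depends on two ICCs that the article does not give and on how many centres join. For hypothesis 2 the distortion is minor within the same ICC range. The direction for environment effects does not depend on the assumed values, as long as both exposure and outcome correlate positively within centres; only the size does.

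**What to change.** 1. Record a centre code with each anonymous response, and name the call-centre as the cluster.
2. For variables that differ between agents, include centre as a fixed effect or centre them on the centre mean.
3. Test centre-level environment variables against between-centre variation with a small-sample reference: t on centres minus 2 degrees of freedom (8 with 10 centres), or a mixed model with the Kenward-Roger correction. Label these effects exploratory if only about 10 centres join.
4. Use cluster-robust standard errors in the SEM, and say that they are themselves unreliable with about 10 clusters, so that steps 2 and 3 carry the inference.
5. Report the ICC of each main score with a confidence interval. The follow-up trial would need it if whole centres are randomised.

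**Cost.** One extra data field, which must be in place before the survey opens, and changes to the analysis text. No extra participants are needed. Intervals will be wider and fewer environment effects will reach significance. Rewording cannot give 10 centres the information of a larger number, so confirmatory claims about centre-level effects would need more centres.

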### Main measurement tool – biopsychosocial questionnaire

A biopsychosocial questionnaire will be developed for the online survey, and based on self-report tools, tested for reliability and validity. This questionnaire will be piloted among a sample of call-agents, different from those participating in the main survey. The questionnaire will include the Voice Symptom Scale (VoiSS) [13], Voice Handicap Index (VHI) [14], and The Vocology Screening Profile [15]. The VoiSS was developed from 800 participants and is psychometrically the most robust and extensively validated self report voice measure available [13]. This scale includes three domains of impairment, physiological and emotional aspects of voice symptoms and is assessed using a 5-item scale (0 = never and 4 = frequently). Example items are 'Do you feel you have to strain to produce voice?' and 'Does your voice make you feel incompetent?'. The VHI was devised by Jacobson and colleagues [14], and it uses a similar measurement 5-item scale. Example items are 'My voice difficulties restrict my personal and social life' and 'My voice problem upsets me'. In addition, the Vocology Screening Profile assesses vocal symptomatology [15]. This uses the same measurement scale and example items include 'Increased effort to talk' and 'Feeling thirsty', relating to physiological, acoustic and vocal function symptoms.

